**Antibacterial and antifungal activity of Halo**

The antimicrobial activity of Halo was evaluated against a panel of aerobic and anaerobic bacteria using M07-A8 and M11-A7methods respectively, as described by the Clinical and Laboratory Standards Institutes (CLSI). A standardized inoculum of bacteria (1 x 10^4^ cells/mL) was incubated with serially diluted solutions of Halo (0.1% CPC, or 1 µg/mL) or chlorhexidine (2% chlorhexidine gluconate, or 20 µg/mL) as comparator. Cells were allowed to grow in the presence or absence (growth control) of the test agents for 24 h. The MIC for each agent was defined as the concentration that induced a 100% growth inhibition (compared to no-drug control). As can be seen in Table 1, Halo exhibited potent activity against *S. salivarius*, *P. gingivalis, S. pyogenes, S. pyogenes, S. pneumonia* (MIC = 0. 98 µg/mL for all), *F. nucleatum* and *S. mutans* (MIC = 1.95 µg/mL against both). The MIC of Halo against *S. oralis* and *S. mitis* was noticeably elevated (500 µg/mL) compared to other organisms. It is interesting to note that *S. oralis* and *S. mitis*, are normal commensals of the oral cavity. In contrast to Halo™, chlorhexidine exhibited activity against both pathogenic as well as commensal oral organisms (MIC = 19.6 µg/mL).

We used a similar microdilution-based CLSI method (M27-A2) to evaluate the activity of Halo against *albicans* and non-*albicans* *Candida* species. Our results showed that the MIC (50% inhibition of growth) of Halo against *C. albicans*, *C. krusei*, *C. tropicalis*, or *C. glabrata* ranged between 0.06 µg/mL and 0.25 µg/mL), while the MIC of chlorhexidine was much higher (19.6 µg/mL, see Table 1). Taken together, these results demonstrate that Halo possesses potent activity against pathogenic bacteria and fungi commonly isolated from the oral cavity. This activity was more potent than that observed for chlorhexidine.

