**Duration of Antimicrobial Activity of Halo™ *in vitro*: Determination of Post-Antimicrobial effect (PAE)**

Post antimicrobial effect (PAE) is defined as suppression of microbial growth that persists after limited exposure to an antimicrobial agent. Having a longer PAE is considered advantageous for antimicrobial agents as it allows for persistent inhibition of microbial growth, and may affect dosing regimens since agents with long PAEs may need less frequent administration than those with short PAEs. Previous studies have described PAE for both antibacterial and antifungal agents [[27-30](#_ENREF_27)]. We evaluated the PAE of Halo™ against oral bacteria (*S. pneumonia*, *S. sanguis*, *S. gordonii* and *S. aureus*). Briefly, cells were exposed to Halo™ (at a concentration equal to the MIC) for 1 min followed by three washes to remove residual drug. Plates were incubated at 37 °C and time taken for the cells to regrow was determined. PAE was calculated as the time difference required for a culture to grow 1 log_10_ following exposure to and removal of Halo™ at its MIC compared to the time required for 1 log_10_ of growth in an unexposed control culture [[28](#_ENREF_28)]. PAE was expressed as the time (in hours) for which growth inhibition (%) was maintained by Halo, compared to untreated control.

| [figure not shown] |
| --- |
| **Fig. 10. Post antimicrobial effect (PAE) of Halo against oral bacteria** |

As shown in Figure 10, the post-antimicrobial effect (PAE) of Halo ranged between 4 h and 24 h against *S. aureus*, *S. pneumonia*, *S. gordonii*, *S. sanguis*, *S. salivarius*, and *S. mitis*. These results show that Halo™ exhibits activity against oral bacterial for 4-24 h.

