Microbial cultures will be performed from oral swabs obtained from enrolled study participants. Briefly, collected swabs will be vortexed in 1 mL saline, and a calibrated 10 µL inoculation loop will be used to spread the resulting suspension (and its serial dilutions) onto agar plates specific for aerobic or anaerobic bacteria (blood agar), or fungi (Sabouraud dextrose). Plates will be incubated at 37 °C overnight and the resulting CFUs will be counted to determine the microbial load.

In terms of safety and tolerance of Halo and placebo, the oropharynx and gingiva will be examined for erythema and ulcerations during each scheduled visit. This will not be pursued at the interim visits when presenting with an acute upper respiratory disease as mucosal changes are likely to be present related to these syndromes. Subjects will be queried about any intraoral or systemic adverse reactions. Toxicity will be graded according to modification of the National Institutes of Health, National Institute of Allergy and Infectious Diseases, DMID Adult Toxicity Tables provided in Appendix 1.

Subjects will keep a daily diary of oral temperature, product usage adherence, typical cold and flu symptoms that may occur, school or work absenteeism, and visits to physicians’ offices, emergency departments and urgent care centers using REDCap electronic data capture tools hosted at University Hospitals Case Medical Center. REDCap (Research Electronic Data Capture) is a secure, web-based application designed to support data capture for research studies. Following the completion of the study, participants will be asked to take a short survey through the same REDCap system in order to assess the acceptability of the product and to gather information about the volunteers’ willingness to continue to use the product beyond the study parameters and if they would recommend the product to others. Finally, to further assess adherence to the study, product bottles will be counted.

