**INVESTIGATIONAL PRODUCTS**

**Study Product Description**

Halo is a proprietary formulation in which a high concentration of a polyvinyl pyrollidone backbone polymer is incorporated into an anionic polymer solution as well as an antimicrobial agent, cetylpyridinium chloride (CPC) at 0.1%. The formulation has high mucoadhesion properties and prolonged retention time in the oral cavity (21). Cetylpyridinium chloride like chlorhexidine is a quarternary ammonium salt antiseptic. Due to its chemical structure, CPC demonstrates significant antiviral activity especially against respiratory viruses (discussed in Preliminary Studies). Toxicology studies have shown no evidence of acute or chronic toxicity in animal models or irritant effect or in human use for the treatment of xerostomia (ref). In this study the placebo will consist of purified sterile water without CPC - the active antiseptic. This placebo was chosen as the Halo formulation without CPC serves to act as a barrier to attachment of oral pathogens, and as such is an important contributing factor to its antimicrobial activity (see above). The use of preservative could be problematic as there may be some anti microbial activity. Without the use of preservatives, the product will be refrigerated except for administration.

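### Culture swabs go into plain saline with no step to neutralise CPC, so residual antiseptic can lower colony counts in Halo swabs only, by an unknown amount

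*Protocol*

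**What the plan says.** Secondary objective 4 (Protocol Schema) is the effect of Halo on oropharyngeal bacteria and fungi. The assay is summarised under Study Outcome Measures: "collected swabs will be vortexed in 1 mL saline, and a calibrated 10 µL inoculation loop will be used to spread the resulting suspension". The same sentence continues "and its serial dilutions) onto agar plates specific for aerobic or anaerobic bacteria (blood agar), or fungi (Sabouraud dextrose", so dilutions are plated as well as the neat suspension. The reading is single: "Plates will be incubated at 37 °C overnight and the resulting CFUs will be counted to determine the microbial load". No neutralising, washing or filtration step is named.

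Study Product Description gives the CPC content of Halo as 0.1% and adds: "The formulation has high mucoadhesion properties and prolonged retention time in the oral cavity". Under Administration, both arms spray three times a day. The placebo is purified sterile water without CPC. The diary captures adherence, but no section sets or records the interval between the last spray and a swab.

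Under Scheduled Follow-up Visits, enrolment and interim-visit swabs are analysed in real time. All other swabs are stored for possible later use, depending on funding.

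**The concern.** An antiseptic carried on the swab keeps acting on the organisms in the tube, because saline dilutes CPC but does not inactivate it. Only Halo swabs taken on treatment can carry it: placebo swabs contain none, and the enrolment swab is taken before any product is used. The error therefore differs between arms, and it would also enter a change from baseline.

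The protocol's own bench work guards against this. In the post-antimicrobial effect experiment, cells were exposed "for 1 min followed by three washes to remove residual drug" before regrowth was timed. The time-lapse microscopy and the antiviral removal experiments also washed the agent off first. The clinical assay has no counterpart.

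The direction of the error matters too. Table 1 MICs are low for Candida and most listed bacteria but 500 µg/mL for S. oralis and S. mitis. Carry-over would thus tend to lower counts of the susceptible species and spare those two commensals, which resembles the selectivity the protocol attributes to Halo. A laboratory contribution could be mistaken for confirmation.

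**Working it through.** **Inputs from the Protocol.** CPC 0.1% (Study Product Description); diluent 1 mL and loop 10 µL (Study Outcome Measures); MICs in µg/mL (Table 1): C. krusei and C. tropicalis 0.06, C. glabrata 0.125, C. albicans 0.25; S. salivarius, P. gingivalis, S. pyogenes and S. pneumoniae 0.98; F. nucleatum and S. mutans 1.95; S. aureus and Y. enterocolitica 3.91; S. oralis and S. mitis 500.

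**Assumptions, not in the Protocol.** Swab pick-up v = 0.1 mL (range 0.05 to 0.2 mL); CPC in oral fluid at swabbing, r = 0.1%, 1% or 10% of product strength; 20 mL agar per plate; overnight = 16 to 24 h.

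**Step 1, units.** 0.1% w/v = 0.1 g per 100 mL = 1000 µg/mL. The antibacterial section prints "0.1% CPC, or 1 µg/mL". That cannot stand beside a measured MIC of 500 µg/mL. The bacterial MICs are also successive halvings of 1000: 1000/2 = 500, 1000/2^8 = 3.91, 1000/2^9 = 1.95, 1000/2^10 = 0.98. I use 1000 µg/mL and take Table 1 as printed.

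**Step 2, undiluted tube.** Concentration = r × 1000 × v / (1 + v). With v = 0.1 mL:

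| Residual r | Oral fluid (µg/mL) | Tube (µg/mL) | Table 1 MICs exceeded |
|---|---|---|---|
| 0.1% | 1 | 1 × 0.1/1.1 = 0.09 | C. krusei, C. tropicalis only |
| 1% | 10 | 10 × 0.1/1.1 = 0.91 | all Candida; just under 0.98 |
| 10% | 100 | 100 × 0.1/1.1 = 9.1 | all except S. oralis, S. mitis |

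**Step 3, residual needed to reach an MIC.** Oral concentration = MIC × (1 + v)/v.
- For 0.98: 0.98 × 1.2/0.2 = 5.88 µg/mL (0.6% of product strength) at 0.2 mL pick-up; 0.98 × 1.05/0.05 = 20.58 µg/mL (2.1%) at 0.05 mL.
- For C. albicans: 0.25 × 6 = 1.5 µg/mL (0.15%) to 0.25 × 21 = 5.25 µg/mL (0.5%).
- For S. oralis and S. mitis: at least 500 × 6 = 3000 µg/mL, three times the neat spray, so not reachable.

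**Step 4, plated dilutions.** Their number and factor are not stated. At 1:10 the residual needed for 0.98 becomes about 6% to 21% of product strength. At 1:100 it becomes 59% to 206%, largely out of reach. Dilution costs sensitivity, however. One colony from 10 µL corresponds to 100 CFU/mL of suspension on the neat plate and 1000 CFU/mL on a 1:10 plate, so an organism between these is expected to be countable only on the least-diluted plate.

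**Step 5, on the plate.** At 10% residual, 10 µL carries 0.01 mL × 9.1 µg/mL = 0.091 µg CPC. Diffused into 20 mL agar this is 0.0045 µg/mL, below the lowest MIC in Table 1. The exposure that matters is in the tube and briefly on the fresh streak.

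**Step 6, timing of the read.** The Protocol concludes: "These results show that Halo™ exhibits activity against oral bacterial for 4-24 h". A 4 h delay leaves 12 to 20 h of a 16 to 24 h incubation; a 24 h delay leaves none. Delayed but viable organisms could therefore be missed at a single overnight count.

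**The case against.** Several points on the other side stand.

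- Plating serial dilutions already mitigates carry-over in part (Step 4), and agar diffusion removes most inhibition on the plate (Step 5). Neither undoes exposure already suffered in the tube.
- MICs are an imperfect yardstick. The bacterial MICs come from 24 h of growth with the agent present and the Candida MICs from 50% inhibition. Neither measures killing during a vortex-and-plate step of unstated length.
- The culture method is given in brief, so a laboratory procedure might add a neutraliser. The method as written nonetheless specifies saline.
- Residual CPC, swab volume and contact time are all unknown, so the effect may be anything from negligible to material.

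A reader might infer something stronger: that a lower count in the Halo arm could be made wholly in the laboratory, so that objective 4 cannot be answered. The documents do not support this. With 0.1 mL pick-up the tube is at 1/11 of the oral-fluid concentration, so organisms inhibited in the tube had already met about 11 times as much CPC in the mouth. The artefact is added to an in-mouth effect and does not replace it.

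Nor can the 4 to 24 h growth delay be charged to the laboratory alone. Bacteria exposed in the mouth would bring it with them as a product effect, and a neutraliser would not remove it. It was reported for bacteria, not Candida, after exposure at the full MIC, which the tube may not reach.

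It would also be too broad to treat every on-treatment swab as affected. Under the current text only interim-visit swabs are cultured on treatment; stored scheduled-visit swabs come into play only if they are cultured later.

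**Conclusion.** The concern holds as a one-sided bias of unknown size in secondary objective 4. As written, the assay lets residual CPC act in the tube for on-treatment Halo swabs and for no others. With no recorded time since last spray, the data could not later show how much of a difference arose there.

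On the stated assumptions, residuals of about 0.15% to 0.5% of product strength bring the undiluted tube to the C. albicans MIC, and about 0.6% to 2.1% bring it to the lowest bacterial MIC. These are small fractions for a product described as long-retained, but the documents give no oral concentration at any time after spraying. The conclusion rests on reading 0.1% as 1000 µg/mL and on Table 1 as printed.

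No primary clinical outcome is touched. This is an inexpensive improvement to one secondary objective of a pilot study.

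**What to change.** In the culture paragraph of Study Outcome Measures, replace saline with a CPC-neutralising diluent for the culture aliquot, in both arms, so that handling is identical and the blind is kept. First run a one-off check that the diluent does not itself inhibit growth. Record the time since last spray at each swab and report CFU by that interval. Apply the same handling to scheduled-visit swabs if they are later cultured. Leave PCR handling unchanged.

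A second, later plate reading is optional: it may recover delayed growth, but it cannot separate laboratory exposure from exposure in the mouth.

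The cost is a different diluent, one validation run and one time field on the case report form. The change leaves dosing and clinical care as they are.

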**Randomization and Withdrawal Procedures**

The randomization list will be generated and provided to the study pharmacist. The study blind (except for the Study Pharmacist) will be maintained by all study personnel. The investigators may request that the blind be broken for medical reasons.

Each subject will be encouraged to complete the full course of the intervention assignment and study assessments. However, it is understood that the subject may discontinue study participation at any time for any reason. In addition, subjects should be encouraged to return to the unit within 28 days after dropout for additional safety assessments. The reason for early withdrawal must be documented in the CRF and in the source documents. Subjects are free to withdraw from the study at any time for any reason. Subjects should normally be withdrawn from the trial if a serious adverse event (SAE) occurs. Exceptions must be discussed with the Sponsor.

Subjects **must** be withdrawn from the trial if:

1. They withdraw their consent;
2. The investigator considers it in the best interest of the subject that he or she is withdrawn;
3. They experience a grade 3 or 4 adverse event (AE) (Appendix 1)

The reason for any subject’s discontinuation and the date of withdrawal will be recorded in the subject’s CRF. The subject’s CRF, which will be completed up to the point of withdrawal. The study report will include reasons for subjects’ withdrawals as well as details relevant to the subjects’ withdrawals. Any subject withdrawn from the trial prior to completion will undergo all procedures indicated in this protocol as being scheduled to occur at discharge or upon early withdrawal, subject to his/her consent. Any subject withdrawn due to an adverse event (whether serious or non-serious) or any clinically significant abnormal laboratory test value will be evaluated by the Principal Investigator or a monitor (see Key Personnel), and will be treated and followed up until the symptoms or values return to normal or acceptable levels, as judged by the Principal Investigator.

Relevant post-study procedures will be performed, wherever possible, on subjects who elect to withdraw. If a subject is withdrawn from participation in the study at any time at his or her request or as determined by the Study Investigators, the reason(s) for discontinuation shall be documented thoroughly in the source documents and CRFs. If a subject is discontinued because of an adverse event, this event will be followed until it is resolved or the subject is clinically stable and will also be documented in the source documents and CRFs.

Subjects who receive any amount of study product and who subsequently withdraw or are withdrawn from the study will be encouraged to continue Follow-up (with subject’s consent) for safety. The subject will be asked for permission to continue scheduled evaluations and complete an end-of study evaluation. If an AE or SAE has occurred, every effort will be made to undertake protocol-specific safety follow-up procedures, and the subjects will be encouraged to receive appropriate care until the signs and symptoms or laboratory toxicities resolve.

**INVESTIGATIONAL PRODUCTS**

**Study Product Description**

Halo is a proprietary formulation in which a high concentration of a polyvinyl pyrollidone backbone polymer is incorporated into an anionic polymer solution as well as an antimicrobial agent, cetylpyridinium chloride (CPC) at 0.1%. The formulation has high mucoadhesion properties and prolonged retention time in the oral cavity (21). Cetylpyridinium chloride like chlorhexidine is a quarternary ammonium salt antiseptic. Due to its chemical structure, CPC demonstrates significant antiviral activity especially against respiratory viruses (discussed in Preliminary Studies). Toxicology studies have shown no evidence of acute or chronic toxicity in animal models or irritant effect or in human use for the treatment of xerostomia (ref). In this study the placebo will consist of purified sterile water without CPC - the active antiseptic. This placebo was chosen as the Halo formulation without CPC serves to act as a barrier to attachment of oral pathogens, and as such is an important contributing factor to its antimicrobial activity (see above). The use of preservative could be problematic as there may be some anti microbial activity. Without the use of preservatives, the product will be refrigerated except for administration.

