**Experimental Design and Methods**

**Overview**

This is a pilot study of the safety, tolerability, and effectiveness of Halo to prevent acute upper respiratory illness and respiratory virus infections. This study will be conducted at one site (University Hospitals Case Medical Center) in healthy adults during the upcoming respiratory virus season. The intervention will be with Halo, a commercial product which is FDA-approved for the treatment of xerostomia. The placebo will consist of purified sterile water without CPC - the active antiseptic. This placebo was chosen as the Halo formulation without CPC serves to act as a barrier to attachment of oral pathogens, and as such is an important contributing factor to its antimicrobial activity (see above). The use of preservative could be problematic as there may be some anti microbial activity. Without the use of preservatives, the product will be refrigerated except for administration.

Male and female participants 18-45 years of age will be recruited and monitored for the development of, duration, and severity of clinical symptoms and signs consistent with acute respiratory disease (defined below) captured daily through diaries, and PCR confirmation of important respiratory viruses including influenza, rhinoviruses, adenoviruses, and respiratory syncytial virus during episodes of acute respiratory disease during the length of the study will be undertaken. Secondary objectives will assess the tolerance, acceptability and adherence to Halo as well as the change in the bacterial (oral streptococci and Group A streptococcus) and fungal microflora in the oropharynx. School or work absenteeism, visits to physicians’ offices, emergency departments and urgent care centers will also be captured. Conventional cultures for these bacterial and fungal organisms will be pursued (see below). Throughout the study period, the safety, tolerability, acceptability and adherence to study products will be assessed.

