**Safety:**

Halo is an oral spray that is intended to provide reduce the microbial load in the oral cavity which may help protect against infections, including respiratory disease. The product has been formulated with a combination of lubricating/hydrating polymers and humectants. It contains 0.1% cetylpyridinium chloride as the active ingredient as well as the excipients, 35% glycerin copovidone, flavor, methylparaben, propylparaben, PEG-60 hydrogenated castor oil, sodium benzoate, sodium saccharin, water, xanthan gum and xylitol. Halo Spray is dosed from a conventional pump spray bottle without the aid of propellants. The consumer is directed to hold the spray bottle upright and to spray six times into the mouth without rinsing or spitting out. The recommended dosage is as required 3 times or 9 sprays per day.

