**Storage**

Halo is stable at room temperature. It can also be stored in the refrigerator (4^O^ C). At both storage temperatures, it was shown that the physical and microbiological are maintained. The Placebo should be stored in the refrigerator (4^O^ C). To maintain the blind both Halo and Placebo will be stored in the refrigerator (4^O^ C).

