**Administration**

Based upon the preliminary studies that assessed the duration of the antimicrobial effects of Halo as reported in the preliminary studies and feasibility, subjects assigned to both study arms will be asked to spray the product intra-orally 3 times daily (Three sprays per use, total = 9 sprays per day). Although it is recognized that respiratory viruses most often and initially invade the nasopharynx (ref), it is still the case that the oropharynx is also involved in the pathogenesis of disease and there may be diffusion to the nasopharynx of orally administered product given the anatomic proximity of these anatomic sites.

As noted above, the study products will be supplied in 30 mL bottles to participants. Product should preferably be administered 30 minutes after any meal or brushing of teeth throughout the day and right before retiring. In between uses, the study product will be kept at room temperature. Subjects will be asked to retain bottles of all study products to be brought to scheduled visits to be counted by study personnel as a measurement of adherence. The date of initial use and the final use will be recorded on each study bottle.

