**Clinical/Laboratory Evaluations and Study Schedule**

**Screening/Enrollment (See Appendix 2, Schedule of Events)**

Written informed consent will be obtained before any clinical evaluations are performed. The study will consist of 2 groups randomly assigned to Halo or matching placebo. The study visits will be conducted in the CWRU School of Medicine Room 3080. Screening and Enrollment will be performed at the same visit, a complete medical history and physical exam will be performed by study clinicians along with, serum chemistries, CBC with differential count, and a serum pregnancy test for women. Randomization into the study will be undertaken when it is determined that the subject has met all study inclusion criteria and has no exclusion criteria other than possible lab results. Since the screening and enrollment will be conducted at the same visit, subjects will begin the study prior to results of labs. If the labs result in an exclusion criteria the subject will be notified to discontinue and return unused study product. As noted in the safety section:. the study product has an acceptable safety profile and poses no significant toxicological risk to individuals. The formulation consists of ingredients with a long history of safe use in oral healthcare products.

A posterior pharyngeal and nasal swab will be obtained to ascertain baseline bacterial and fungal organisms and a multiplex PCR for respiratory viruses. Study product (after randomization) will be provided until the next scheduled visit, study procedures will be again reviewed, contact information for reaching study personnel will be provided, and study diaries will be distributed. Appointments for the 1^st^ monthly evaluation will be made.

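### The trial is described as double-blind with a matching placebo, but the placebo is plain water against a flavoured, sweetened, mucoadhesive spray, so participant blinding is not assured; the storage instructions also conflict.

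*Protocol*

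**What the plan says.** **Blinding.** The Protocol Schema describes a randomized, double-blinded, placebo-controlled trial. The Screening/Enrollment section says participants are "randomly assigned to Halo or matching placebo".

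**Placebo.** The Study Product Description says: "In this study the placebo will consist of purified sterile water without CPC - the active antiseptic". The Overview says the same. Both give the reason: "This placebo was chosen as the Halo formulation without CPC serves to act as a barrier to attachment of oral pathogens". Both add that preservative might itself have antimicrobial activity.

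**Halo.** Besides 0.1% cetylpyridinium chloride (CPC), the Safety section lists "35% glycerin copovidone, flavor, methylparaben, propylparaben, PEG-60 hydrogenated castor oil, sodium benzoate, sodium saccharin, water, xanthan gum and xylitol". The Study Product Description adds that the formulation adheres strongly to mucosa and stays in the mouth for a long time.

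**Storage.** The Study Product Description, like the Overview, says: "Without the use of preservatives, the product will be refrigerated except for administration". The Storage section says: "To maintain the blind both Halo and Placebo will be stored in the refrigerator". The Administration section says: "In between uses, the study product will be kept at room temperature".

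**Outcomes.** Under Study Outcome Measures, participants record symptoms and their duration, a daily 5 p.m. temperature, absenteeism and care visits in a REDCap diary. Under Interim Visits, they are to contact staff within 72 hours of onset.

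**The concern.** A double-blind claim assures the reader that participants cannot tell which product they have. Here the two products, as described, differ in flavour, sweetness and mouth-feel, and each participant uses one of them three times a day for 75 days. The only step described to keep the products alike is refrigerating both.

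The outcomes exposed are the primary ones. A participant who believes they have the active spray may record fewer or shorter symptoms, or be slower to call the site. One who believes they have water may do the reverse. A difference between arms could then partly reflect belief rather than protection.

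The storage conflict is a separate matter. The protocol gives refrigeration as the consequence of leaving out preservative, and the placebo is the product without it. An instruction to keep bottles at room temperature between uses takes away that safeguard.

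**Working it through.** The protocol gives no figure on blinding, so there is none to reproduce. The check compares passages, followed by one illustration.

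**1. Is the placebo matched as described?**

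| Property | Halo | Placebo |
|---|---|---|
| Flavour | Yes (Safety; Toxicological Risk Analysis) | None listed |
| Sweetener | Saccharin, xylitol (Safety) | None listed |
| Glycerin, gum, polymer | Yes (Safety; Study Product Description) | None listed |
| Preservative | Parabens, benzoate (Safety) | None |
| Refrigerated | Yes (Storage) | Yes (Storage) |

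The products are aligned only on storage. The stated reasons cover leaving out the vehicle (barrier effect) and the preservative (possible activity). Neither reason addresses whether participants can tell the products apart.

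**2. Which outcomes depend on the participant?**
- The illness definition needs a temperature above 37.8°C, a non-productive cough and at least two of four listed symptoms. The participant takes the temperature and records the symptoms.
- Duration comes from the diary.
- The interim visit, with its clinician examination and swab, takes place only if the participant calls.
- Under Scheduled Follow-up Visits, only enrollment and interim swabs are analysed in real time. The others are stored for later use that depends on funding. PCR results during illness therefore also depend on the call.

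**3. Do the storage passages agree?**
- The Overview and Study Product Description keep the unpreserved product cold apart from when it is being used.
- Administration keeps study product at room temperature between uses. With three uses a day, that is nearly all the time.
- These cannot both be followed for the placebo. The Storage section does not settle it, because it can be read as covering storage before dispensing.

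**4. How much could reporting bias matter? (illustration)**

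Inputs from Sample Size Calculations: control mean 2 events, SD 1, alpha 0.05, 51 per arm. My assumptions: a two-sided test (the protocol does not say), all 51 per arm analysed, no true effect, and a fraction *b* of episodes unreported in the Halo arm. The protocol gives no value for *b*.

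Apparent difference: δ = 2*b*. Standard error: √(2 × 1²/51) = 0.198. Chance of a significant result in favour of Halo: 1 − Φ(1.96 − δ/0.198).

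| *b* | δ (events) | Chance of a significant result for Halo |
|---|---|---|
| 0% | 0 | 2.5% |
| 5% | 0.1 | 7% |
| 10% | 0.2 | 17% |
| 15% | 0.3 | 33% |
| 20% | 0.4 | 52% |
| 25% | 0.5 | 71% |

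For *b* = 10%: 0.2/0.198 = 1.01, 1.96 − 1.01 = 0.95, and 1 − Φ(0.95) = 0.17. The last row equals the planned effect of 0.5 events.

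**The case against.** The choice of water is reasoned. The protocol explains twice why it avoids the CPC-free vehicle and preservative, and its own laboratory work supports caution: the Halo vs. placebo experiments report a 1.0 log fall in viral load from the preservative-containing placebo. An inert comparator is a legitimate aim, and this point does not dispute it. Nor does it follow that the placebo must be flavoured and sweetened. That would leave mouth-feel different. It could also add active compounds, since the flavours include essential oils and the direct-antiviral experiments report some activity from other components of the formulation. It is a trade-off for the sponsor.

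It can also be said that unblinding is not shown. This is a parallel-group trial, each participant receives one product, and nothing says that they know Halo's taste or can compare. That is correct: a reader might infer that participants will recognise their product at first use, and the protocol does not establish it. What stands is narrower: the protocol claims matching and describes nothing that achieves it.

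The outcome has some protection from the fever criterion, the clinic visit with examination, and PCR, which is already planned. These limit the bias but do not remove it, because the temperature is self-taken and the visit is participant-triggered.

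Finally, a reader might infer that room-temperature storage will contaminate the placebo, raise its culture counts and favour Halo. The protocol has no data on growth in the bottles or on whether growth would alter swab counts. The storage point stands only as a contradiction.

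**Conclusion.** The concern holds in this form: the double-blind and matching descriptions are not supported by the products as described, participant blinding is not assured, and the primary illness outcomes are open to reporting bias. The bias plausibly favours Halo, but neither direction nor size is established. The 7% to 71% range rests on an assumed shortfall of 5% to 25% and shows only that modest reporting differences would matter at this sample size. It is not an estimate for this trial.

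That Halo adheres and has a distinctive feel is read from its ingredients and stated mucoadhesion; the protocol reports no taste or texture comparison.

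The storage passages contradict each other for the unpreserved placebo. This review takes no position on which instruction is right.

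**What to change.** 1. In Screening/Enrollment, drop the word matching. There and in the Protocol Schema, say that the placebo is water and that blinding of participants is not assured.
2. Add one item to the end-of-study REDCap survey already planned under Study Outcome Measures, asking which product the participant believes they had and why (taste or feel, or perceived benefit). Report the answers by arm and interpret the diary-based results in that light.
3. Present the already planned PCR-confirmed episodes beside the diary-based result, noting that these too depend on the participant calling the site.
4. Reconcile the Overview, Study Product Description, Storage and Administration sections into one storage instruction for both arms.

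The cost is one survey question, some rewording and a less favourable description of the blinding. Reformulating the placebo is not required.
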